### Sample size considerations

Data from a cohort study among primary school children under the care of the Cardiff and Vale University Health Board CDS was used to derive the caries incidence in children (mean age 6.5yrs) with at least one erupted first permanent molar [23]. These data showed that 40% had caries in one or more of their first permanent molars by the age of 10. Based on recent Cochrane reviews it is estimated that FV would reduce the 3 year incidence from 40% to 30% in this population [7], whereas PFS would reduce it further to 20% [6]. For an individually randomised trial at a power of 80% with a significance level of 5%, at least 313 children per group are required for a comparison of 20% vs 30% at 3 year follow-up.

The following assumptions have been made to ensure the necessary recruitment and retention: 3560 parents will be invited to consent to their child’s participation in the trial, associated with an estimated 55% refusal rate. Experience from the existing programme shows that 2% of consented children will refuse to cooperate to allow PFS placement and an estimated 1% will be excluded on medical grounds. An anticipated 40% of consented children will lack an erupted FPM and therefore be ineligible for randomisation.

The above attrition is estimated to leave 920 participants to be randomised to the technologies being evaluated (460 per arm). An 8% (n=204) per annum loss to follow-up has been assumed based on the current programme and a previous cohort study [23]. Finally a 5% absence at the final examination has been assumed, leaving 680 children for analysis at the final examination.

### Research governance / ethical considerations

Given the extensive clinical experience and relatively low risk nature of the two interventions under evaluation, several aspects of the MHRA/DH/MRC guidance on risk-based approaches to the management of Clinical Trials of Investigational Medicinal Products (CTIMPS) [24] were employed in the design and implementation of this trial (specifically, with regards to IMP management and adverse event reporting). Furthermore a risk-based approach to the informed consent process was developed in collaboration with a parent's group from a representative participant population [25].

Full ethical approval for this study has been obtained from the Research Ethics Committee for Wales (Ref: 11/MRE09/06). The study will be conducted in compliance with the following:

• Declaration of Helsinki [26]

• ICH Harmonised Tripartite Guideline for Good Clinical Practice [27]

• The Medicines for Human Use (Clinical Trials) Regulations 2004 (Statutory Instrument 2004 No. 1031) as amended by the Medicines for Human Use (Clinical Trials) Amended Regulations 2006 (Statutory Instrument 2006 No. 1928 and No. 2984) and Amended Regulations 2008 (Statutory Instrument 2008 No. 941) [28].

• Research Governance Framework for Health and Social Care (Welsh Assembly Government 2nd Edition, September 2009 and Department of Health 2nd Edition, July 2005) [29].

Two external bodies; a Data Monitoring and a Trial Steering Committee, will monitor study progress.

### Adverse events

The procedure for reporting adverse events arising as a result of participation in the trial is show in Figure 3.

**Figure 3 F3:**
[figure not shown]
Flow chart for Adverse Event Reporting Procedures.

### Statistical analysis

The primary outcome measure will be the presence or absence of dental caries on any of the first permanent molars included in the trial at 36 months. Secondary outcomes include patient, hygienist and nurse rated treatment acceptability as well as sealant retention for those children in the sealant arm. Outcome measures for the health economic analysis include Health Related Quality of Life and Quality Adjusted Tooth Years.

### Primary outcome measurement

The presence or absence of dental caries and caries treatment on all surfaces of all teeth will be recorded using the ICDAS system [13]. Summed counts of surfaces and teeth with disease and or treatment are computed from these data. Counts for first permanent molars included in the trial will be calculated. These counts are then converted into a binary outcome at child level. The proportion of participants with any treated or untreated caries (at ICDAS level 4) in the first permanent molars included in the trial at the final follow-up examination will be compared between the two trial arms.

ICDAS equivalents to conventional DMFT (D3 caries into dentine level) will be calculated for the primary analysis; caries at earlier stages (level 2 and 3) will be used for secondary analysis of the primary outcome. Caries counts for the whole mouth will also be calculated for use in further exploratory analyses.

### Secondary outcome measurement

Patient rated treatment acceptability will be measured using the Delighted-Terrible (D-T) faces scale. This scale consists of five items rated 1–5 relating to the participants experience of treatment. The D-T scale score will be calculated as the sum of valid responses for individual items divided by the number of valid responses.

The hygienist and nurse rated treatment acceptability will be measured using the Adverse Outcomes (A-O) scale. This scale consists of 6 items scored 0–1. The A-O scale score will be calculated as the sum of valid responses for individual items divided by the number of valid responses.

The retention of sealants in the sealant arm will be derived from the treatment records. The proportion of sealants retained intact and partially intact will be reported at 1 year, 2 years and 3 year time points.

The presence and severity of hypomineralisation/hypoplasia in the first permanent molars will be recorded at each dental examination and the prevalence reported by treatment arm. Severely hypoplasic teeth will be excluded from the trial.

### Descriptive analysis

#### Analysis of primary outcome

The primary outcome for this study is the presence of filled or unfilled caries (at ICDAS level 4) on any 1 of up to 4 teeth included in the trial per child. As such the primary outcome is binary at child level. Logistic regression will be used to determine the difference between treatments. Covariates to be included in the primary model will include those variables used to balance the randomisation (gender and baseline caries) as well as the number of designated study teeth per child. Adjusted and unadjusted odds ratios from the logistic regression will be reported, the adjusted analysis will be taken as the primary outcome.

Since children for this study are to be recruited from schools there may be some possibility of school clustering effects. Schools are likely to be similar in terms of caries risk since they are all designated Community First schools, however multilevel modelling will be used to account for possible clustering at school level. ICC values will be reported.

The Complete Case (CC) population will be used for the primary outcome analysis.

#### Analysis of secondary outcomes

The distribution of the Patient Rated Treatment Acceptability (D-T) score and the Adverse Outcomes score will be examined for departures from normality. Rating scales typically exhibit positive skew however small departures from normality do not preclude parametric methods. Negatively skewed data will be transformed such that it conforms to a normal distribution.

Linear regression analysis will be used to model the difference between scores for the treatment groups. Covariates to be considered for inclusion in the model are gender, baseline caries, fluoride use, oral hygiene regimen and dietary sugar intake. Adjusted and unadjusted effect sizes and confidence intervals will be reported. The primary analysis for secondary outcome will be the adjusted analysis.

The data will be examined for possible school cluster effects and if significant, a 2-level linear regression analysis will be used to adjust for clustering. ICC values will be reported.

Appropriate summary measures for the scores will be reported in tables in original (untransformed) scale. Effect sizes and confidence intervals will be back transformed if required for ease of interpretation.

For those children in the sealant arm of the trial, sealant retention will be examined and reported. Secondary outcomes analysis will use the treatment groups as randomised using the CC population.

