#### Medical history and caries risk related habits

The medical history of the child will be ascertained by asking the parents to complete a medical history form, which will collect data specifically relating to: allergies; asthma (including whether this has resulted in hospitalisation); sensitivity to constituents of either PFS or FV; if the child is currently participating in a clinical trial involving an IMP. Whether or not the child is registered with a General Dental Practitioner will also be ascertained.

Following enrolment onto the trial, any changes to the child’s relevant medical history (as described above) will be identified by enclosing a brief Medical History Follow-Up Form with the postal questionnaires sent to parents on an annual basis during the trial.

For children deemed eligible to participate in the trial, information relating to caries risk related habits will be obtained via a postal questionnaire sent to parents at baseline, 12, 24 and 36 months post treatment.

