### Randomisation

Randomisation of participants will be stratified by school and balanced for gender and baseline caries levels using minimisation in a 1:1 ratio for treatments. An additional random component will be added to the minimisation algorithm [22] such that it is not completely deterministic. Randomisation will be undertaken by SEWTU remote from the trial sites.

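### The acceptability analyses adjust for school only after a significance test, and their transformation rules can yield effect sizes that are not in scale points

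*Protocol article*

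**What the plan says.** The section Analysis of secondary outcomes covers two scores defined under Secondary outcome measurement. The Delighted-Terrible faces score is the mean of five items rated 1 to 5. The Adverse Outcomes score is the mean of six items scored 0 or 1. Both are to be modelled by linear regression.

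- **School.** The data are examined for clustering and, "if significant, a 2-level linear regression analysis will be used to adjust for clustering". The section Analysis of primary outcome has no such condition: "multilevel modelling will be used to account for possible clustering at school level". The section Randomisation says: "Randomisation of participants will be stratified by school and balanced for gender and baseline caries levels using minimisation in a 1:1 ratio".
- **Transformation.** The article expects rating scales to be positively skewed, then says: "Negatively skewed data will be transformed such that it conforms to a normal distribution". No transformation is named, and nothing is said about transforming positive skew.
- **Back-transformation.** "Effect sizes and confidence intervals will be back transformed if required for ease of interpretation". Summary tables are to stay on the original scale.
- **Covariates.** "Covariates to be considered for inclusion in the model are gender, baseline caries, fluoride use, oral hygiene regimen and dietary sugar intake". The adjusted analysis is the main one, and unadjusted results are reported as well.

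**The concern.** Acceptability is a stated secondary objective, and the Background names patient acceptability among the criteria by which varnish might be judged an acceptable alternative to sealant. The size of the difference between arms should therefore be readable in the units of the scale and come from a model fixed in advance.

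The rules as written work against this in two ways. First, a stratification factor is kept or dropped on the result of a test, so two equally valid data sets could be reported from different models. The primary and secondary analyses would also treat the same design feature differently. Second, a non-linear transformation followed by inversion of the estimated difference does not return a difference in points, and the same holds for its confidence limits. The trigger is also odd, because it acts on the direction of skew that the article does not expect.

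**Working it through.** **Which sample applies.** The article gives no figure for the acceptability outcomes. Its 680 is the number expected at the 36-month caries examination: 920 × (1 − 0.92³) = 204 lost, 920 − 204 = 716, and 716 × 0.95 = 680, which reproduces the text. The faces score is completed straight after the first application and at each follow-up visit (Process evaluation), so up to 920 children contribute at first treatment.

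**How often the school test is significant.** Inputs: 66 schools and 920 children (article); a one-way ANOVA F test at 5%, equal school sizes and the ICC values are assumed.
- Children per school: m = 920/66 = 13.94. Degrees of freedom: 65 and 920 − 66 = 854. Critical value: 1.321.
- With ICC ρ, the F ratio is distributed as k times a central F, where k = 1 + mρ/(1 − ρ). Power = P(F > 1.321/k).

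| ICC | k | 1.321/k | Power |
|---|---|---|---|
| 0.02 | 1.284 | 1.029 | 42% |
| 0.03 | 1.431 | 0.923 | 65% |
| 0.05 | 1.734 | 0.762 | 92% |

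With 680 children the same formula gives 29%, 47% and 77%, but that number belongs to the final examination.

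**What omitting school costs.** With 1:1 allocation within schools, the true variance of the difference rests on the within-school share, 1 − ρ, while a model without school uses the total. The reported standard error is too large by 1/√(1 − ρ): 1.010 at ρ = 0.02, 1.026 at 0.05 and 1.054 at 0.10.

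**What the pre-test does to inference.** This was simulated with 66 schools of 14 children, randomised within school, with school fixed effects standing in for the 2-level model and ICC from 0 to 0.2. The mean estimate was about 0 under the null, and 0.185 to 0.187 for a true effect of 0.185. Type I error under the test-first rule was 4.7% to 5.7%. The 5.7% arose at ICC 0.2, where the test was always significant, so the rule coincided with always adjusting. Ignoring school was mildly conservative (3.3% at ICC 0.2).

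**Back-transformation of a faces score.** Scores were simulated as the mean of five correlated 1–5 items with negative skew (−0.77 and −0.47). The arm means were 4.15 and 3.83, a true difference of 0.32.
- Square: mean squares 17.685 and 15.225, difference 2.460; √2.460 = 1.57.
- Reflected square root, √(6 − x): means 1.338 and 1.451, difference 0.113; 0.113² = 0.013.
- Reflected log, ln(6 − x): means 0.550 and 0.713, difference 0.163; e^0.163 = 1.18, a ratio of geometric means of reflected scores.
- Back-transforming each arm's mean and then subtracting: 0.30 (square) or 0.32 (reflected square root).

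A second set of assumed scores, with a true difference of 0.40, gave the same pattern: about 1.75, about 0.02 and a ratio of about 0.82 (there taken in the opposite direction). Confidence limits fare no better: squaring a limit loses its sign, and a negative limit has no square root.

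**Direction of skew.** Replacing x by 6 − x reverses the sign of the skew and nothing else. The article does not say whether delighted is scored 1 or 5, so the coding alone could decide whether the same answers are transformed.

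**Adverse Outcomes score.** If each of six signs occurs independently in a proportion p of children (assumed), the share scoring zero is (1 − p)^6 and the skew is (1 − 2p)/√(6p(1 − p)). At p = 0.03 these are 83% and +2.2; at p = 0.10 they are 53% and +1.1. The skew is positive, so the stated rule leaves this score untransformed.

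**The case against.** The strongest reply is that little is at risk. Children are randomised individually within school, so the pre-test leaves the estimate unbiased and type I error near 5%, and the ICCs it tends to miss are those where omission matters least. This stands. A reader might infer from the pre-test that the treatment effects themselves could be wrong; the design and the simulation do not support that.

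A reader might also infer that the Adverse Outcomes score is the worst case, transformed and then back-transformed to a severely distorted difference. The rule does not do this: a mostly-zero score is positively skewed and is not transformed. Linear regression on it is imperfect, but the mean difference remains interpretable.

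For the faces score, transformation depends on negative skew and back-transformation on need. The method is unnamed and may be settled in the analysis plan. A log transformation would give a legitimate ratio, and original-scale summaries would sit beside any odd effect size. All this makes the harm possible rather than certain. It does not rescue the rule, which says that effect sizes and intervals are back-transformed, and unadjusted summaries do not supply an adjusted difference with its interval.

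Finally, it is tempting to say that the analysed sample will shrink, because habit data "will be obtained via a postal questionnaire sent to parents at baseline, 12, 24 and 36 months post treatment" and the analysis is complete-case. But these covariates are only candidates, the return rate is not given, and unadjusted results are also reported. The final set can fairly be left to the analysis plan.

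**Conclusion.** The point holds as a modest, nearly free improvement to rules that the article states.

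- **School pre-test:** inconsistent with the stratified randomisation and with the primary analysis. Its fault is that chance selects the model, with detection of 42% to 92% for ICC 0.02 to 0.05 at 920 children. It does not cause bias, and omitting school makes the standard error about 1% to 5% too large for ICC 0.02 to 0.10. The article gives no ICC, so these values are assumptions.
- **Transformation and back-transformation:** the trigger does not match the skew that the article expects and depends on scoring direction. If a faces score is transformed, inverting the difference does not give scale points: a true 0.40 became about 1.75 or 0.02, or a ratio of about 0.82. These figures rest on assumed score distributions, but the failure to return points follows from any non-linear transformation.

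Only secondary outcomes are touched. The primary analysis and the sample size are unaffected.

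**What to change.** In Analysis of secondary outcomes, or in the analysis plan:

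1. Include school, with gender and baseline caries, in every acceptability model, without a pre-test. Continue to report the ICC.
2. Delete the transformation and back-transformation rules. Report the mean difference on the original scale, with a robust or bootstrap interval that respects school.
3. Optionally, add any adverse sign (yes/no) as a supporting analysis of the Adverse Outcomes score. This is a preference, not the correction of an error.
4. If questionnaire habits are used as covariates, confine them to a sensitivity analysis, so that children whose parents did not reply stay in the main one.

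The cost is wording and minor analysis work, with no new data and no change to the sample size.

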#### Secondary analysis of primary outcomes

An exploration of child and school level characteristics will be carried out using a 2-level logistic regression model. School level factors include size of school, postcode and participation in the oral health education programme. Child level factors include data collected from parent interviews on fluoride toothpaste use, oral hygiene routine and dietary sugar habits as well as Welsh Index of Multiple Deprivation [30].

Secondary analysis of the primary outcome will also be carried out as a per-protocol analysis on those participants who attend all treatment sessions (baseline and 5x6montly appointments where required) irrespective of randomisation assignment. Any dose response for number of fluoride treatment applications and sealant retention time on the primary outcome will also be investigated.

Multi-level regression analysis will also be carried out using tooth level data. A 2- or 3- level logistic regression model with tooth, child and possibly school will be used to examine caries incidence in the first permanent molars. Tooth levels factors such as upper or lower arch as well as child level factors will be included.

An investigation of the treatment differences on the earlier development of caries will also be examined using level 2 and 3 of the ICDAS classification of caries.

Data entry, management and analysis will be conducted centrally at the South East Wales Trials Unit (SEWTU).

### Time plan for the SoV trial

Participant recruitment began in July 2011 and is planned to continue to until December 2012. Children will be followed up for three years and therefore the last child will have their final follow-up assessment in December 2015.

## Discussion

The study will be conducted in primary schools in South Wales. Under the umbrella of the Welsh Oral Health Action Plan, the Community Dental Service (CDS) in Cardiff and Vale University Health Board delivers a primary school based PFS placement programme (‘Designed to Smile’) to approximately 3,300 6 year-olds annually. This programme, and its predecessor, have been in place since 2002. The programme involves Community First Schools, so designated by the Welsh Government on the basis of the high socioeconomic deprivation status of the school catchment area. The prevalence of dental caries in these areas is amongst the highest in the United Kingdom [31]. Permission to adapt the Designed to Smile programme for the purposes of this trial has been granted by the Chief Dental Officer for Wales.

A schools-based programme, utilising mobile dental clinics, is considered to have several advantages over conducting the proposed research in general dental practices.

The Designed to Smile programme is established and gives access to a cohort of high-risk children, experiencing the necessary burden of disease to allow an appropriate test of the technologies. This setting accesses children who might not otherwise routinely attend a general dental practice - attendance being linked to socioeconomic status [32]. In addition to having the necessary throughput of patients to achieve the required recruitment rate of at-risk children (as defined by SIGN / BSPD guidelines [10,11]), a schools-based setting will facilitate control over retention and follow-up. Furthermore, and perhaps most importantly, the CDS has established a relationship with the schools, parents and the children over many years which will obviously facilitate meaningful user and participant involvement in the study. In addition to service user representatives, staff involved in the existing CDS programme were consulted during the design and work-up of this trial, ensuring that it will be implemented and conducted in a way that is empathetic to the needs of the participating children, their parents and their schools.

On the basis that we are testing the relative clinical and cost-effectiveness of two established technologies, both of which have been proven clinically effective against placebo treatments [6,7], this trial will not contain a placebo control arm.

The objectives of this study have been identified by the National Institute for Health Research as one of importance to the National Health Service in the UK.
